## Introduction

### Background

Neuropathic pain (NP) is one of the most frequent spinal cord injury (SCI) complications, with the most negative impact on quality of life [1]. Patients with NP show significant differences in quality of life when compared to those without it [2]. The prevalence of NP secondary to SCI varies depending on the population characteristics, chronicity of the lesion, and the criteria of defining it. In a meta-analysis, the prevalence of NP in patients SCI was 53% (95% CI 38.58-67.47) [3], with a prevalence of 47.8% being observed in Cali, Colombia [4-6]. Pain, quality of life, and functionality are proven to be associated, and patients with secondary NP to SCI are affected in these areas [7,8], thus limiting participation in daily activities and self-care. Chronic pain has an effect on emotional state, as well as cognition, in regard to pain anticipation, which can further lead to catastrophization.

The term “pain catastrophization” is of a recent use, consisting of three components: rumination (putting excessive focus on the painful sensation), magnification (exaggerating the damage), and perception of inability to control the symptom [9]. Different strategies have been proposed to alleviate the complications of SCI [10-12]. The pharmacological management of patients with NP secondary to SCI is widely known, and there is increasing evidence of anticonvulsant and antidepressant use for its management [13,14]. Nevertheless, the nonpharmacological management is not fully elucidated since the efficacy is inconclusive. Previous studies reported interventions such as transcranial electrical stimulation, acupuncture, and transcutaneous electrical nerve stimulation [15,16], which improved NP in patients with SCI; however, more evidence on other nonpharmacological interventions is needed.

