### Assignment of Interventions

The groups compared in this study are the intervention (hydrotherapy) and control (standard physical therapy) groups. This control group was chosen as the current standard of care for nonpharmacological management of NP in SCI is physical therapy [30-32].

Participants will be assessed as follows: at the beginning of the intervention (baseline; Time 1) and at the end of the intervention (4 weeks after discharge; Time 2). Table 1 describes the schedule with procedures and the assessments scales in the trial timeline.

**Table 1 table1:** Schedule of enrollment and assessments.

Time point (T)		T1: baseline (week 0)	T2: follow-up (week 4)

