## Discussion

### Expected Findings

The expected main findings of this study are as follows: (1) effects on minimizing disability and improving quality of life between current standard and novel hydrotherapeutic approach are comparable; (2) hydrotherapy is a safe, efficient, and effective alternative to the current management of NP secondary to SCI; (3) given a choice, patients are more likely to choose hydrotherapy rather than the current standard of care if both options are presented to them. To our best knowledge, this is the first trial that proposes to evaluate the effects of hydrotherapy in the NP reduction in Latin America.

The purpose of rehabilitation is to maximize patients’ daily functional independence through a goal-oriented treatment [55]. Heterogenous results from previous hydrotherapeutic studies on patients with diabetic or other metabolic neuropathies do not allow for definitive conclusions [56]. Conversely, the hydrotherapeutic approach for patients with peripheral neuropathies has yielded positive results on gait and balance, which, besides pain, are the most commonly presented symptoms in our patient cohort [6,57].

The presence of a control group is necessary, since there are no currently available nonpharmacological treatments with evidence for NP management in patients with SCI. The pilot trial design with parallel groups aims to provide preliminary evidence on the clinical efficacy of hydrotherapy on NP secondary to SCI, with a single-masked study design being performed in order to alleviate bias. Consideration of a DN-4 score of ≥4 out of 10 for the identification of NP and mixed pain syndromes [39] ensures adequate screening in our trial population. This questionnaire has been suggested for epidemiological studies, where accurate identification of NP symptoms is also crucial to test in order improve therapeutic approaches.

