### Conclusions

Hydrotherapy is likely to be a safe, efficient, and cost-effective alternative to the current standard of care for NP secondary to SCI, with comparable results between the two.

Since this is a pilot trial, randomized controlled trials with calculated power levels and sample sizes will be warranted in order to provide conclusive answers on noninferiority or superiority of the proposed treatment effect.

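### Similar results against a physical therapy control of unproven effect cannot show that hydrotherapy reduces neuropathic pain, yet the article's conclusions lean that way

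*Protocol article*

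**What the plan says.** **The control.** Assignment of Interventions compares hydrotherapy with standard physical therapy, on the ground that "the current standard of care for nonpharmacological management of NP in SCI is physical therapy". These are the only two arms.

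**Evidence for treatments of this kind.** Expected Findings justifies having a control group because "there are no currently available nonpharmacological treatments with evidence for NP management in patients with SCI". The Background is milder: "the nonpharmacological management is not fully elucidated since the efficacy is inconclusive". It also names three other nonpharmacological treatments (transcranial electrical stimulation, acupuncture and transcutaneous electrical nerve stimulation), "which improved NP in patients with SCI".

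**The aim.** The main hypothesis (Primary and Secondary Objectives) is that hydrotherapy reduces neuropathic pain after SCI.

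**The reading of results.** Expected Findings anticipates comparable effects on disability and quality of life and, as a separate item, that "hydrotherapy is a safe, efficient, and effective alternative to the current management of NP secondary to SCI". The Conclusions of the abstract and of the Discussion go further. They say hydrotherapy is likely to be a safe, efficient and cost-effective alternative for this pain, and attach to that a statement that the two treatments give comparable results. The Discussion's Conclusions then call for later powered trials "in order to provide conclusive answers on noninferiority or superiority of the proposed treatment effect".

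**The concern.** A two-arm comparison shows how much better or worse one treatment is than the other. It shows whether the new treatment works at all only if the control's own effect is known, or if the new treatment wins. The article expects the arms to look alike, describes the evidence for the control's class of treatment as absent or inconclusive, and still concludes in favour of hydrotherapy.

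At stake is the answer to the main hypothesis. A small between-arm difference reported as support for an effective alternative would be a positive claim resting on a result that is equally expected if neither treatment does anything for pain. The Limitations section covers the single centre, loss to follow-up and masking, but not this.

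**Working it through.** The main point is one of logic, and no figure in the article is wrong. The planned size of 20 is 10 + 10, taken from a pilot-study recommendation (Sample Size and Power Calculation). No effect size, SD, power or margin lies behind it, so there is nothing further to reproduce.

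**Step 1: what the design can identify.** Let H be the true pain reduction due to hydrotherapy against no treatment, P the same for physical therapy, and N the change that would occur anyway (natural course, regression to the mean, and the pain medication and extra physical therapy that Interventions allows in either group).
- Change in the hydrotherapy arm = H + N
- Change in the physical therapy arm = P + N
- Difference between arms: D = H − P

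There are two observed quantities and three unknowns. Only D is identified, and H = D + P.

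**Step 2: put in the expected result.** If D = 0, then H = P.
- If physical therapy works (P > 0), hydrotherapy works equally well.
- If physical therapy does nothing for this pain (P = 0), hydrotherapy does nothing either.

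The data look the same in both cases. Improvement from baseline in both arms does not separate them, because N appears in both. More participants sharpen D but say nothing about P.

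**Step 3: the informative result.** If D > 0 in favour of hydrotherapy, and physical therapy does no harm (P ≥ 0), then H > 0. A between-arm difference therefore does bear on the main hypothesis.

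**Step 4: would similarity even be established?** Inputs: 10 versus 8 participants (Results), a two-sided α of .05 (Effectiveness of the Intervention), and an assumed NPRS SD of 1.5 to 3 points, since none is given. As a simple approximation, take a two-sample comparison of change or follow-up scores:

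half-width = t(0.975, n1 + n2 − 2) × √(1/n1 + 1/n2) × SD

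| Arms | Half-width in SD units | NPRS points, SD 1.5 | NPRS points, SD 3 |
|---|---|---|---|
| 10 vs 10 (planned) | 2.101 × 0.447 = 0.94 | 1.41 | 2.82 |
| 10 vs 8 (recruited) | 2.120 × 0.474 = 1.01 | 1.51 | 3.02 |

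Power at 10 versus 8 (noncentral t) is about 17% for a true difference of 0.5 SD and 35% for 0.8 SD. It reaches 80% only at about 1.4 SD. A nonsignificant difference is thus likely even when a sizeable one exists in either direction.

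For scale, a noninferiority comparison with one-sided α of 0.025, 80% power and a true difference of 0 needs n per arm = 2 × (1.960 + 0.842)² / margin², with the margin in SD units. Assumed margins of 0.3, 0.5 and 0.8 SD give 175, 63 and 25 per arm.

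**The case against.** **Standard of care need not be proven care.** A reader might infer that the article contradicts itself three ways about its control. The text does not support that. A treatment can be customary and unproven, so the reason given for choosing physical therapy and the statement in Expected Findings can both be true. The treatments that the Background credits with benefit do not include physical therapy, so that sentence says nothing about the control. It conflicts only with the sweeping form of "there are no currently available nonpharmacological treatments with evidence for NP management in patients with SCI", and the Background's own word, inconclusive, is close to it. The references cited for physical therapy are not at hand, so its true evidence base cannot be judged here.

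**Comparable is limited in one place.** Expected Findings confines it to disability and quality of life and lists effectiveness separately, so that list alone does not derive effectiveness from comparability. This stands. The two Conclusions sections carry no such limit and attach comparable results to care for the pain itself.

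**Nothing in the Methods reads similarity as efficacy.** This is correct. The analysis sections specify a two-sided test and a model to estimate the effect of hydrotherapy, and the problem sits in expectations and hedged conclusions. The article also calls itself a pilot, performs no power calculation and leaves firm answers to later trials. That lowers the weight of the point but does not remove it, because the conclusion is stated regardless and the pilot's declared aim includes preliminary evidence of efficacy.

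**A usual-care comparator is legitimate.** Agreed. The lack of an untreated arm is not a fault in itself; it limits what a similar result can mean.

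**Conclusion.** The point holds in a limited form. A similar result in the two arms cannot support the hypothesis that hydrotherapy reduces neuropathic pain, because the article does not treat its control's effect on this pain as shown and has no arm that would reveal it. Sample size does not affect this. With 10 versus 8 participants and no margin, similarity itself would be uncertain by about ±1.0 SD (±1.5 to ±3.0 NPRS points under the assumed SDs).

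The problem arises only if the arms turn out alike, which is what the article's conclusions expect. A difference favouring hydrotherapy would still be informative, provided physical therapy does not worsen the pain.

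Two stronger readings should be set aside. One is that the statements about the control flatly contradict each other; they are loosely worded and need aligning. The other is that a later noninferiority trial against physical therapy could never be justified. The article sets no margin and leaves both options open, so the sound position is that such a trial would first need evidence that physical therapy reduces this pain.

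**What to change.** 1. In Expected Findings, align the statement on evidence for nonpharmacological treatment with the Background (inconclusive) and with the reason given for the control in Assignment of Interventions, so that the article makes one consistent statement of what is known about physical therapy for this pain.
2. In the abstract's Conclusions, Expected Findings and the Discussion's Conclusions, add a sentence such as: *Only a between-group difference in NPRS favouring hydrotherapy will be taken as preliminary evidence of an effect on pain; a similar result in the two groups leaves effectiveness unknown and will be reported as an estimate with its 95% CI.*
3. Remove the sentence in both Conclusions sections that joins a favourable verdict on hydrotherapy to comparable results.
4. Make any noninferiority aim for the next trial conditional on evidence that physical therapy reduces this pain.

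The cost is wording only; no endpoint, analysis or trial conduct changes, and recruitment has already closed. The downside is a more modest claim if the arms turn out alike.

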### Limitations

This study has some limitations. Given the single-center design of our study, the generalizability of our results will be limited. Even though we have accounted for patients lost to follow-up, true percentages might be higher than expected, therefore skewing our findings. Despite the advantages of a single-masked trial design, double-masked trials are prone to less pitfalls [60].

### Conclusions

Hydrotherapy is likely to be a safe, efficient, and cost-effective alternative to the current standard of care for NP secondary to SCI, with comparable results between the two.

Since this is a pilot trial, randomized controlled trials with calculated power levels and sample sizes will be warranted in order to provide conclusive answers on noninferiority or superiority of the proposed treatment effect.

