**Objective:**

We hypothesize that (1) hydrotherapy is effective in reducing NP secondary to SCI. Additionally, our secondary hypotheses are that (2) hydrotherapy decreases the catastrophization of NP, and that (3) hydrotherapy improves life quality and minimizes the degree of disability, when compared to physical therapy.

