### Primary and Secondary Objectives

The main study hypothesis is that (1) hydrotherapy is effective in reducing NP in patients with SCI. Additionally, our secondary hypotheses are that (2) hydrotherapy decreases the catastrophization of neuropathic pain, and that (3) hydrotherapy improves life quality and minimizes the degree of disability, when compared to the other physical therapy techniques.

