### Statistical Analysis

#### Sample Size and Power Calculation

In order to demonstrate recruitment feasibility, 20 participants will be enrolled (10 per group) in accordance with sample size recommendations for pilot studies [53]. As this is a pilot study, power calculations were not performed.

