#### Effectiveness of the Intervention

Treatment effects will be derived using longitudinal modeling of within-person change in mean scores of the scales and subscales’ scores from baseline to follow-up. Baseline characteristics of participants in both groups will be compared using the chi-square or 2-tailed Fisher exact test for categorical variables, and the Student *t* test or Wilcoxon test for continuous variables, after assessing the tests’ assumptions. Statistical significance will be set at a 2-tailed α of .05, expressed as a 95% CI.

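### The article forecasts comparable, cost-effective and patient-preferred hydrotherapy, but it hypothesises superiority on quality of life and disability, sets no margin, and lists no cost or preference outcome

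*Protocol article*

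**What the plan says.** **Hypothesis.** In the Abstract (Objective) the third hypothesis is that "hydrotherapy improves life quality and minimizes the degree of disability, when compared to physical therapy". Primary and Secondary Objectives repeats it: "hydrotherapy improves life quality and minimizes the degree of disability, when compared to the other physical therapy techniques".

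**Forecast.** Expected Findings lists first that "effects on minimizing disability and improving quality of life between current standard and novel hydrotherapeutic approach are comparable", and third that, "given a choice, patients are more likely to choose hydrotherapy" over the current standard.

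**Conclusion.** The Conclusions section of the Discussion says: "Hydrotherapy is likely to be a safe, efficient, and cost-effective alternative to the current standard of care for NP secondary to SCI, with comparable results". The Abstract's Conclusions carries the same statement. In the Discussion, the next paragraph leaves conclusive answers on noninferiority or superiority to later trials with calculated power. The Abstract has no such caveat.

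**Inference.** Effectiveness of the Intervention gives the only decision rule for the comparison: "Statistical significance will be set at a 2-tailed α of .05, expressed as a 95% CI". The Abstract's Methods plans group means and their differences with 95% CIs and P values. No equivalence or noninferiority margin is stated.

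**Outcomes.** The Abstract, Table 1 and Data Collection name the pain rating scale (NPRS), the catastrophizing scale, the SF-36 and the WHODAS 2.0. Data Collection adds the ASIA impairment scale.

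**Size.** "In order to demonstrate recruitment feasibility, 20 participants will be enrolled", 10 per group, with no power calculation because this is a pilot. Results reports 18 recruited: 10 to hydrotherapy and 8 to physical therapy.

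**The concern.** The article points in two directions on the same two outcomes. Under the third hypothesis, success on quality of life and disability means that hydrotherapy does better. Under the first expected finding, it means that the arms look alike. With both in print, a significant result and a null result could each be presented as what the investigators expected.

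The null result is the more troublesome. A test of difference that fails to reach significance does not show similarity unless the interval is narrow enough to exclude differences that matter, and no such difference has been named. In a trial of this size the interval will be wide.

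Cost-effectiveness and patient preference raise a simpler problem. They are claims about quantities that are not among the listed outcomes, so no result of this trial could confirm or refute them.

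**Working it through.** **Step 1. The plan's own figure.** The planned 20 comes from pilot-study recommendations. No effect size, SD, power or margin lies behind it, so there is no calculation to reproduce. Omitting one is acceptable in a pilot. The question is what 18 people can say about comparability.

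**Step 2. Precision of the between-arm difference.** Inputs: 10 and 8 participants (Results), two-sided .05 (Effectiveness of the Intervention). For an unadjusted two-sample comparison, in SD units:

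half-width = t(.975, n1+n2−2) × √(1/n1 + 1/n2)

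- 10 vs 8: 2.120 × √(0.100 + 0.125) = 2.120 × 0.474 = **1.01 SD**
- 10 vs 10 as planned: 2.101 × √0.200 = 2.101 × 0.447 = **0.94 SD**

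The article gives no SD. If the NPRS SD is assumed to lie between 1.5 and 3 points, 1.01 SD is about ±1.5 to ±3.0 points on a 0 to 10 scale. The first expected finding concerns quality of life and disability, for which the SD-unit figure is the relevant one.

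An observed difference of exactly zero would thus leave about 1 SD in either direction within the interval.

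**Step 3. How often a real difference is missed.** Noncentral t, 16 degrees of freedom, two-sided .05, 10 vs 8:

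| True difference | Power | Nonsignificant |
|---|---|---|
| 0.5 SD | 17% | 83% |
| 0.8 SD | 35% | 65% |
| 1.0 SD | 51% | 49% |

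Power of 80% requires a true difference of about 1.42 SD.

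**Step 4. What a noninferiority claim would need.** The margins are assumed, since none is given. One-sided .025, true difference zero, margin m in SD units. For 80% power:

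n per arm = 2 × (1.960 + 0.842)² / m² = 15.7 / m²

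| Assumed margin | n per arm for 80% power | Power with 10 vs 8 |
|---|---|---|
| 0.3 SD | 175 | 9% |
| 0.5 SD | 63 | 17% |
| 0.8 SD | 25 | 35% |
| 1.0 SD | 16 | 51% |

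**Step 5. The planned model.** Analysis of Outcomes specifies a random effects model over two time points, not an unadjusted comparison. If its treatment effect is the difference in change from baseline, with equal variances at both times and correlation ρ between them, the half-width is multiplied by √(2(1−ρ)). The article does not state ρ. For illustration:

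- ρ = 0.5: 1.01 × √1.0 = 1.01 SD
- ρ = 0.7: 1.01 × √0.6 = 0.78 SD

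The figures in Steps 2 to 4 are therefore approximate for the planned analysis.

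**Step 6. Claims against outcomes.** None of the instruments named in the Abstract, Table 1 or Data Collection is presented as a measure of cost or of choice between therapies. The participant questionnaire is an appendix that is not shown, but neither the text nor Table 1 names an outcome of either kind.

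**The case against.** **These are hedged forecasts, and the article limits them itself.** The concluding sentence speaks of likelihood, and the other items stand under Expected Findings. The Discussion calls the evidence preliminary and reserves noninferiority and superiority for powered trials. This stands, and it lowers the severity. It does not remove the contradiction with the third hypothesis, it gives no support to the cost and preference statements, and it is absent from the Abstract.

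**No rule equates nonsignificance with similarity.** A reader might infer that a P value above .05 will be reported as proof of comparability, or that comparability could rest on nothing else. The documents do not support either inference. No such rule is written, and the Abstract's Methods plans differences with 95% CIs, from which similarity could be judged informally. What remains is that an interval of this width would rarely allow that judgement.

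**Not every hypothesis is plainly comparative.** The first two say that hydrotherapy is effective on pain and decreases catastrophization. Whether the comparator phrase governs them is unclear. The explicit contradiction is confined to quality of life and disability, which are secondary outcomes.

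**Similarity might mean that neither therapy works.** A reader could infer this from the remark that "there are no currently available nonpharmacological treatments with evidence for NP management in patients with SCI". The article is not consistent here: Assignment of Interventions presents physical therapy as the current standard of care, with citations, and the Background reports other nonpharmacological interventions that improved this pain. The point does not rest on that inference.

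**The arithmetic is not that of the planned model.** This is correct. The figures describe an unadjusted comparison and are approximate for the longitudinal model.

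**Conclusion.** The point holds as a fault of wording that affects what the trial may conclude. It should be fixed, but it does not undermine the design.

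- The third hypothesis and the first expected finding contradict each other on quality of life and disability.
- With 10 vs 8 and no margin, a nonsignificant difference could not support comparability. The unadjusted half-width is about 1.0 SD. The planned model may narrow this, depending on the unstated correlation. The NPRS conversion and the margins used above are assumptions.
- Cost-effectiveness (both Conclusions sections) and patient preference (Expected Findings only) correspond to no listed outcome, whatever the sample size.

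Three stronger readings go too far. The article does not conclude that patients prefer hydrotherapy; it lists this as an expectation. A nonsignificant result is not certain to be the likeliest one: that depends on the true effect, and it ceases to be so once the difference reaches roughly 1 SD. The feasibility basis for the sample size does not require feasibility to replace the declared primary outcomes.

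**What to change.** - In the Abstract's Conclusions and the Discussion's Conclusions, delete the cost-effectiveness claim and the statement of comparable results.
- In Expected Findings, delete the preference forecast and recast the first item to agree with the third hypothesis, for example: *the trial will give preliminary estimates of whether hydrotherapy improves quality of life and reduces disability more than physical therapy does.*
- Add one sentence, in the Abstract as well as the main text, saying that the between-arm differences and 95% CIs already planned will be read as preliminary estimates for a later trial, and that no claim of similarity or noninferiority will be made from a nonsignificant P value.
- Leave the declared primary outcomes unchanged.

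The cost is wording only: no new data, participants or analyses. The downside is a more modest conclusion.
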